## Abstract

**Background:**

Diabetes is predicted to increase in incidence by 42% from 1995 to 2025. Although most adults with diabetes seek care from primary care practices, adherence to treatment guidelines in these settings is not optimal. Many practices lack the infrastructure to monitor patient adherence to recommended treatment and are slow to implement changes critical for effective management of patients with chronic conditions. Supporting Practices to Adopt Registry-Based Care (SPARC) will evaluate effectiveness and sustainability of a low-cost intervention designed to support work process change in primary care practices and enhance focus on population-based care through implementation of a diabetes registry.

**Methods:**

SPARC is a two-armed randomized controlled trial (RCT) of 30 primary care practices in the Virginia Ambulatory Care Outcomes Research Network (ACORN). Participating practices (including control groups) will be introduced to population health concepts and tools for work process redesign and registry adoption at a meeting of practice-level implementation champions. Practices randomized to the intervention will be assigned study peer mentors, receive a list of specific milestones, and have access to a physician informaticist. Peer mentors are clinicians who successfully implemented registries in their practices and will help champions in the intervention practices throughout the implementation process. During the first year, peer mentors will contact intervention practices monthly and visit them quarterly. Control group practices will not receive support or guidance for registry implementation. We will use a mixed-methods explanatory sequential design to guide collection of medical record, participant observation, and semistructured interview data in control and intervention practices at baseline, 12 months, and 24 months. We will use grounded theory and a template-guided approach using the Consolidated Framework for Implementation Research to analyze qualitative data on contextual factors related to registry adoption. We will assess intervention effectiveness by comparing changes in patient-level hemoglobin A1c scores from baseline to year 1 between intervention and control practices.

**Discussion:**

Findings will enhance our understanding of how to leverage existing practice resources to improve diabetes care in primary care practices by implementing and using a registry. SPARC has the potential to validate the effectiveness of low-cost implementation strategies that target practice change in primary care.

**Trial registration:**

NCT02318108

**Electronic supplementary material:**

The online version of this article (doi:10.1186/s13012-015-0232-2) contains supplementary material, which is available to authorized users.

## Background

Diabetes is the seventh leading cause of death in the United States and currently affects more than 25 million US adults, resulting in total related health costs of more than $170 billion annually [1-7]. Many diabetic complications could be prevented with improved management of glycemia, blood pressure, and lipids. However, this management remains suboptimal in many primary care settings where diabetes care suffers from ‘clinical inertia’ or the failure to appropriately intensify treatment by adding new treatments to achieve control of glycemia, hypertension, and dyslipidemia [8-17]. Because most patients with diabetes and other chronic conditions seek care from primary care practices, improving care in these settings will have a large impact on reducing diabetes-related excess morbidity and mortality and may also help control the costs of diabetes [18]. However, primary practices often lack an effective infrastructure for systematically monitoring their patients’ achievement of diabetes treatment goals to ensure that they are adhering to clinical guidelines [19].

The Chronic Care Model (CCM) is a population-based approach to care delivery that, after it is adopted, can enhance the abilities of primary care practices to improve adherence to clinical guidelines and outcomes by standardizing care delivery [20,21]. This process involves the implementation of registries, which allow practices to better track and monitor the care needs of their patients, providing the opportunity to identify and address clinical inertia among patients with diabetes [22]. The CCM supports the coordinated care that is a key aspect of the patient-centered medical home (PCMH) [23] model, the implementation of which has been shown to improve outcomes for patients with diabetes [24-26]. Unfortunately, a recent study of PCMH implementation in Virginia found that only 1% of practices were able to fully meet all PCMH requirements [27-29]. Most Virginia-based practices had introduced some elements of the PCMH model into their practice but had not focused on using the electronic health record (EHR) effectively for population-based care. For example, the study reported that only 33% of primary care practices in Virginia actively use their EHR for population management tasks such as those supported by registry usage [27-29]. This demonstrates that even those practices that have been able to achieve PCMH transformation have difficulty making population-based care a meaningful part of their everyday practice.

Transformational change that the implementation of CCM and PCMH requires often is overwhelming for primary care practices that are burdened by a payment system that has not consistently supported care management work. With recent changes to the US Medicare payment system (and to some systems of private payers as well), primary care practices will now have the opportunity to be compensated for chronic care management services [30,31]. Even with these changes to the payment system, however, many primary care practices do not have structures in place to easily make changes to care delivery or work processes to support monitoring of patients with chronic illness. For these PCMH and care management innovations to benefit patients with diabetes, these practices likely will struggle to adopt and implement new workflows that focus on addressing patient care needs and clinical inertia [24,27,32,33].

### SPARC: a low-cost intervention to facilitate population-based care

The Supporting Practices to Adopt Registry-Based Care (SPARC) intervention aims to help primary care practices in Virginia develop a population-based care delivery approach to improve care and outcomes for their patients with diabetes. SPARC provides basic support to practices to enable them to implement workflow changes to develop a diabetes registry and use it to manage and improve the care their patients receive. We define a diabetes registry as a searchable list of all patients in a practice who have type 2 diabetes that can be used to monitor patient records and identify gaps in care, lack of adherence to clinical guidelines, or potential instances of clinical inertia, to support patient outreach between scheduled office visits. Diabetes registries typically include clinical and administrative information. Clinical information commonly includes hemoglobin A1c levels, blood pressure, lipid levels, and preventive health screening information for all patients with diabetes. Administrative information varies more widely, but it often includes the date of each patient’s last visit and available demographic information, such as contact information, race and ethnicity, gender, and family supports. The SPARC intervention will focus on supporting practices’ development and use of diabetes registries for proactive care management to help patients achieve better diabetes control and prevent avoidable complications.

SPARC supports practices by advising them on registry development and helping them use existing resources to make workflow changes for successful registry implementation and use. Previous studies have focused on ensuring registry adoption through reliance on outside change agents, such as expert facilitators and evaluators [34-36]. However, interventions that rely exclusively on external resources require consistent funding support for these resources after the project ends. Helping practices use their own internal resources encourages sustainable practice-level innovation that can support problem-solving beyond the initial focus of this study on registry implementation and use. This approach also allows practice members to have complete control over their decisions, as well as flexibility to adapt the registry intervention so it will work best for their practice. Through the careful use of limited support resources, SPARC is designed to be low cost and to yield context-specific solutions, thereby increasing its replicability in a variety of settings. SPARC has the potential to affect the design of future interventions by validating the effectiveness of such low-resource implementation strategies that target practice change in primary care.

### Foundational research

Critical elements of the SPARC intervention were first identified through two previous studies. The Translating Research Into Action for Diabetes study found that improvements in processes of diabetes care (such as ensuring routine, periodic measurement of A1c) were not necessarily associated with improvements in intermediate clinical outcomes (such as A1c levels). Therefore, practice-level efforts to improve care for patients with diabetes will need to move beyond ensuring adequate monitoring alone to a more proactive focus on improving the management of care and appropriate treatment intensification for these patients—that is, a focus on acting on those measurements, when appropriate [37-39]. In addition, we pilot tested the feasibility of a low-cost approach to facilitate diabetes registry implementation and use through the Organizational Self-Assessment to Improve Diabetes Care in Primary Care Practices (R34DK075417) study, referred to hereafter as the R34 pilot study or the R34 study. In that study, six primary care practices worked to implement and use a diabetes registry. Four practices successfully implemented a diabetes registry and increased the percentage of their patients with HbA1c ≤ 7.0 from 77.4 to 79 (*p* = 0.001), with nonsignificant improvements in the percentage of patients with appropriate control of LDL and blood pressure.

Since the completion of the prior pilot study, there have been advances in EHR capabilities, and their use has continued to increase among primary care practices. For example, EHRs certified by the Office of the National Coordinator for Health Information Technology as meeting the standards for the Meaningful Use program sponsored by the Centers for Medicare and Medicaid Services must have registry functionality available as either a built-in function or an add-on module [40]. Therefore, practices participating in SPARC may be able to use EHR-based registry functions not available at the time of the previous pilot study. If participating SPARC practices have an EHR with registry functionality, the SPARC research team will encourage them to use that function. Otherwise, the research team will offer information on how to use a free manual registry software program.

### Study aims

The SPARC study will test a diabetes registry implementation intervention that provides low-intensity technical assistance and peer mentor support to primary care practice-level leaders as they focus on improving the quality of diabetes care in their practices. We will evaluate the effectiveness and cost-effectiveness of SPARC using the methods described below.

The SPARC study has the following aims:Aim 1: Conduct a randomized clinical trial to evaluate the effectiveness of a multifaceted work process redesign intervention for the implementation and use of a diabetes care registry in primary care practice.Aim 2: Evaluate the effect of the intervention on diabetes processes of care and patient outcomes.Aim 3: Evaluate the costs and cost-effectiveness of the intervention in primary care practices.Aim 4: Conduct a qualitative evaluation of the intervention implementation to fully understand the factors associated with success.

## Methods

SPARC is a two-armed RCT comparing the intervention condition of low-intensity technical assistance and peer mentor support for implementing a diabetes registry with the control condition of basic education on population health. We will evaluate the clinical effectiveness and cost-effectiveness of a low-cost intervention for implementing diabetes registries in primary care practices. This study was reviewed by the Virginia Commonwealth University (VCU) Institutional Review Board (IRB) and deemed exempt, because it presents minimal risk to participants and will not be collecting identifiable data on human subjects. SPARC is funded by the National Institute for Diabetes and Digestive and Kidney Diseases and is conducted jointly by researchers in the Department of Family Medicine and Population Health of VCU and Mathematica Policy Research. The New England IRB has reviewed and approved this study.

### Setting and recruitment

The intervention will target 30 Virginia internal medicine and family medicine practices participating in the Virginia Ambulatory Care Outcomes Research Network (ACORN) [41]. ACORN, sponsored by VCU, is a practice-based research network of nearly 100 primary care practices. Member practices are in rural, urban, and suburban settings and range from single-clinician practices to large practice groups and hospital-owned clinics. ACORN member practices choose which studies to be involved in and receive no specific benefit as part of their membership, other than the opportunity to contribute to advancing the science of primary care.

Practices eligible to participate in SPARC must meet the following criteria: (1) the practice must treat adult patients with type 2 diabetes, (2) the clinicians and staff in the practice must be able to change workflows in support of the intervention, and (3) the practice must have a clinician champion who can attend champion meetings (described below) and lead registry implementation in the practice. Practices already using a registry or those that do not currently use an EHR are excluded from participation.

### Randomization

To ensure a balance between the intervention and control groups of practices on the key practice characteristics of setting (rural or urban), size (fewer than three, versus three or more, clinicians), and ownership type (independent or group), the 30 practices were divided into the eight strata formed by these three characteristics and then randomized with equal probability between intervention and control using a random number generator, with 15 practices allocated to the intervention group and 15 to the control group. Each practice was assigned a study identification number upon allocation. Once a year, participating practices will provide the SPARC research team with the total number of adult patients with type 2 diabetes in their practice. Using that number as an upper threshold, a biostatistician on the SPARC research team will generate 100 random numbers for each practice. This number list will be used to identify 100 patient medical records for review in each practice.

### Sample size and power analysis

For evaluating intervention effectiveness, we will review 100 patient records in each of the 30 practices at baseline and 1- and 2-year follow-up intervals. We will draw independent random samples of patient records for each of these reviews, and data will be recorded without patient identifiers. Because patients are not recruited and are not the subjects of the intervention, patient dropout is not a significant issue.

The primary outcome variable is patients’ hemoglobin A1c levels. The research team obtained data on patient hemoglobin A1c levels from practices that participated in the R34 pilot, finding a mean of 7.1, a standard deviation of 1.6, and an intraclass correlation coefficient of 0.065, providing 80% power to detect a 0.5-level decrease in mean hemoglobin A1c from baseline to 1 year in the intervention arm as opposed to the control arm, allowing for up to 20% or six of the participating practices to drop out. If fewer practices drop out of the study, we will have 80% power to detect 15% improvement in the percentage of patients with LDL < 100 (from 53% at baseline to 61% at follow-up), a 20% increase in the percentage of patients with BP < 130/80 (42.2% baseline, 50.6% follow-up), and a 25% increase in the percentage of patients in each practice with HbA1c < 7 (59.2% to 74%). The anticipated baseline rates for these outcomes are derived from baseline rates observed in the pilot study practices.

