### Outcomes

#### Statistical analysis

We will assess intervention effectiveness by comparing the change in patient-level hemoglobin A1c scores from baseline to year 1 between intervention and control practices. A linear mixed-effects model will be used to account for the continuous repeated-measure response (A1c), a fixed-effect group indicator (two levels: intervention, control), a fixed-effect time indicator (two levels: baseline, year 1), and an interaction of the group and time indicators. A practice-level random effect will be included to account for intracluster correlation. Any adjustments to this model for patient- or practice-level characteristics will be made by including those measures as fixed effects. We will analyze secondary effectiveness measures using similar linear mixed-effects models of numerical and categorical measurements, including whether diabetes patients met targets for blood pressure control or LDL cholesterol.

We will assess intervention maintenance of the change in A1c scores using a similar model, with the time periods changing to baseline and year 1, and year 1 to year 2. We will assess practice-level implementation and maintenance using *t*-tests for unadjusted comparisons and using analysis of covariance to adjust differences for practice characteristics. We will categorize practices according to their allocated group, regardless of compliance (intention-to-treat analysis) [45].

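### The power figures do not match the planned change-from-baseline contrast and do not fit together on the inputs given; the LDL and blood pressure claims are unsupported at the only ICC stated

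*Protocol article*

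**What the plan says.** All the power figures stand in Sample size and power analysis. The sampling is "we will review 100 patient records in each of the 30 practices at baseline and 1- and 2-year follow-up intervals", with a fresh random sample of records at each review. The pilot inputs for hemoglobin A1c are given as "finding a mean of 7.1, a standard deviation of 1.6, and an intraclass correlation coefficient of 0.065". The article describes these as "providing 80% power to detect a 0.5-level decrease in mean hemoglobin A1c from baseline to 1 year in the intervention arm", relative to the control arm, allowing six of the 30 practices to be lost.

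It then claims 80% power, if fewer practices are lost, for three binary outcomes: LDL < 100 ("from 53% at baseline to 61% at follow-up"), BP < 130/80 (42.2% to 50.6%) and HbA1c < 7 (59.2% to 74%). No separate ICC is given for any of them.

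The Statistical analysis section sets the primary comparison as "comparing the change in patient-level hemoglobin A1c scores from baseline to year 1 between intervention and control practices". The model has group, time and their interaction as fixed effects, and a single practice-level random effect.

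**The concern.** The article describes the primary effect as a difference in change but gives only the inputs of a cross-sectional comparison. A difference in change between independent samples from the same practices needs one further input: how strongly a practice's effect at baseline correlates with its effect a year later. Without it, the power of the planned contrast cannot be worked out.

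The binary claims raise a second question. LDL, BP and HbA1c < 7 have similar binomial variances, yet all three are said to have 80% power, for differences of 8, 8.4 and 14.8 points. One ICC and one method cannot produce that.

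What is at stake is how results are read. If the LDL and BP comparisons are much weaker than stated, a null result on either could be taken as evidence of no effect when the trial could not have seen one of that size.

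**Working it through.** **Inputs from the article.** SD 1.6; ICC 0.065 (A1c only); m = 100 records per practice per review; 15 practices per arm (Randomization), or k = 12 per arm after an even loss of six. **Assumed:** two-sided alpha 0.05. **Not given, so shown as a range:** CAC, the correlation of a practice's effect between baseline and year 1.

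**1. Reproducing the A1c figure.**
- Design effect = 1 + 99 × 0.065 = 7.435.
- Effective n per arm = 12 × 100 / 7.435 = 161.4.
- SE = 1.6 × √(2/161.4) = 0.178; 0.5/0.178 = 2.81.
- Power = Φ(2.81 − 1.96) = 80.2%. With t on 22 df it is 76.5%.

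This comparison uses year-1 data only and has no baseline term.

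**2. The planned contrast for A1c.** With independent patients at each time,

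Var = (4 × SD² / k) × [ICC × (1 − CAC) + (1 − ICC)/m].

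At k = 12 and a difference of 0.5:

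| CAC | SE | Power (z) | Power (t, 22 df) |
|---|---|---|---|
| 0 | 0.252 | 51% | 47% |
| 0.5 | 0.189 | 75% | 71% |
| 0.8 | 0.138 | 95% | 93% |
| 1 | 0.089 | >99% | >99% |

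Power is 80% at a CAC of about 0.57 by z and 0.62 by t. CAC 1 is what a model with only a practice intercept implies, since it has no practice-by-time term.

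**3. LDL and BP by the method of step 1, ICC 0.065, all 30 practices.**
- LDL: 0.53 × 0.47 + 0.61 × 0.39 = 0.487. SE = √(0.487 × 7.435 / 1500) = 0.0491. 0.08/0.0491 = 1.63, so power is 37%.
- BP: 0.422 × 0.578 + 0.506 × 0.494 = 0.494. SE = 0.0495. 0.084/0.0495 = 1.70, so power is 40% (39.4% with pooled variance).
- Detectable difference at 80%: (1.96 + 0.84) × 0.0491 = 0.138, about 14 points; BP is the same to rounding.
- HbA1c < 7, variance sum 0.434, difference 14.8 points: 89% with 15 per arm and 81% with 12.

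Ignoring clustering altogether gives above 99% for LDL and BP, so that does not explain the stated 80%. With 15 per arm, 80% needs about 600 effective records per arm for LDL and 553 for BP:
- LDL ICC = (1500/600 − 1)/99 = 0.015.
- BP ICC = (1500/553 − 1)/99 = 0.017.

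**4. LDL and BP on the planned contrast, ICC 0.065, 15 per arm.** Same form as step 2, with the binomial variance in place of SD² (z):

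| CAC | LDL | BP |
|---|---|---|
| 0 | 21% | 23% |
| 0.57 | 37% | 40% |
| 0.8 | 55% | 59% |
| 1 | 90% | 92% |

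At the CAC that makes the A1c figure 80%, LDL and BP stand at 37% and 40%. At CAC 1 they exceed 80%, but A1c power is then above 99%, so the stated primary 80% no longer describes the planned contrast.

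**The case against.** The strongest reply has four parts.

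- **A numerical match does not identify the formula.** A change analysis with a CAC of about 0.57 gives the same 80%, and a condensed article need not print its formula. This stands: the article cannot be said to have used a follow-up-only calculation, only that its stated inputs suffice for that one and not for the planned one.
- **No primary deficit follows.** Under the practice-intercept-only model in Statistical analysis, power for 0.5 is well above 80%. This stands too. A reader might infer from the low end of the range that the trial is underpowered for A1c. The documents do not support that, because they give no CAC.
- **The 37% and 40% borrow an ICC reported for A1c only.** The pilot also measured LDL and blood pressure control, so smaller outcome-specific ICCs may have been used. This stands as a limit: the claims cannot be reproduced, but they are not shown to be wrong. It does not make the published figures fit together, since the article gives specific 80% claims alongside one ICC that does not yield them.
- **The 37% and 40% in step 3 use a contrast that is not the planned one.** This carries less weight, because step 4 gives the same two figures on the planned contrast at the CAC that yields the primary 80%.

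A reader might also see a contradiction between the 59.2% base rate for HbA1c < 7 and the pilot result in Foundational research, "7.0 from 77.4 to 79". It is not one. The latter uses a cut-off of at or below 7.0 in the four practices that implemented a registry; the former is strictly below 7 and is attributed to the pilot practices generally. Both the threshold and the set of practices differ.

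**Conclusion.** The point holds as a mismatch and an internal inconsistency. It does not establish that the trial is too small. For the contrast the article plans, the primary power lies anywhere from 51% to above 99% by z with 12 practices per arm, and the stated 80% is right only at a CAC of about 0.57 (0.62 by t). The LDL and BP claims fall to 37% and 40% at the only ICC given, by the calculation that returns the primary figure. At ICC 0.065, no single CAC makes both those claims and the primary claim equal to 80%.

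This rests on two-sided 0.05, an even loss of practices, a common CAC across outcomes in step 4, and the use of the A1c ICC for LDL and BP. The last assumption matters most: ICCs near 0.015 and 0.017 would restore the two secondary claims with all practices retained. The correction is worth making, chiefly for the reading of null LDL and BP results. It does not put the primary analysis in doubt.

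**What to change.** Restate power for the group-by-time contrast at 12 and 15 practices per arm, using t degrees of freedom, over a stated range of CAC, and state alpha. If the pilot's repeated data allow an estimate of the CAC, use it to centre the range.

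For LDL and BP, state the ICC that was used and restate the detectable differences for the planned contrast. If 0.065 was meant to apply, the follow-up-only detectable difference is about 14 points, not 8 and 8.4. Leave the 59.2% base rate as it is on this account.

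The cost is recalculation and restated figures, some of which may be less favourable. No practices need to be added, and the design and data collection do not change.
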